# Web-Based Intervention to Act for Weight Loss in Adults With Type 2 Diabetes With Obesity (Chance2Act): Protocol for a Nonrandomized Controlled Trial

**DOI:** 10.2196/48313

**Published:** 2024-01-31

**Keywords:** readiness to change, behavior change, diabetes, overweight, weight reduction, eHealth, obesity

## Abstract

**Background:**

In adults with type 2 diabetes (T2D), weight loss can improve hemoglobin A_1c_, blood pressure, and triglycerides, and reduce the frequency of medications needed. Unfortunately, a large proportion of these individuals are not ready to initiate weight efforts, making existing obesity management strategies less effective. Many digital health interventions aim at weight loss, but there is still limited evidence on their effectiveness in changing weight loss behavior, especially in adults with T2D.

**Objective:**

This study aims to develop and validate “Chance2Act,” a new web-based intervention, designed specifically to facilitate behavioral change in adults with T2D with obesity who are not ready to act toward weight loss. Then, the effectiveness of the newly developed intervention will be determined from a nonrandomized controlled trial.

**Methods:**

A web-based intervention will be developed based on the Transtheoretical Model targeting adults with T2D with obesity who are not ready to change for weight loss. Phase 1 will involve the development and validation of the web-based health intervention module. In phase 2, a nonrandomized controlled trial will be conducted in 2 government health clinics selected by the investigator. This is an unblinded study with a parallel assignment (ie, intervention vs control [usual care] with an allocation ratio of 1:1). A total of 124 study participants will be recruited, of which 62 participants will receive the Chance2Act intervention in addition to the usual care. The primary outcome is the changes in an individual’s readiness from a stage of not being ready to change (precontemplation, contemplation, or preparation stage) to being ready for weight loss (action stage). The secondary outcomes include changes in self-efficacy, decisional balance, family support for weight loss, BMI, waist circumference, and body fat composition.

**Results:**

The phase 1 study will reveal the intervention’s validity through the Content Validity Index and Face Validity Index, considering it valid if both indices exceed 0.83. The effectiveness of the intervention will be determined in phase 2, where the differences within and between groups will be analyzed in terms of the improvement of stages of change and all secondary outcomes as defined in the methodology. Data analysis for phase 2 will commence in 2024, with the anticipated publication of results in March 2024.

**Conclusions:**

If proven effective, the result of the study may give valuable insights into the effective behavioral modification strategies for a web-based intervention targeting adults with T2D with obesity but not yet ready to change for weight loss. This intervention may be replicated or adopted in different settings, focusing on behavioral modification support that patients need. This study offers a deeper understanding of the application of behavior change techniques for a more holistic approach to obesity care in T2D.

**Trial Registration:**

ClinicalTrials.gov NCT05736536; https://clinicaltrials.gov/study/NCT05736536

**International Registered Report Identifier (IRRID):**

DERR1-10.2196/48313

## Introduction

Obesity has become one of the leading global health concerns over the last century. Numerous studies have proved the complex relationship between obesity and type 2 diabetes (T2D). The majority of patients with T2D are either overweight or obese, thus increasing their long-term risks of developing cardiovascular diseases and diabetes complications [1]. The World Health Organization (WHO) has reported that around 2.8 million people die each year as a result of being overweight or obese [2]. In patients with T2D, weight loss can improve hemoglobin A_1c_, blood pressure, triglycerides, and health-related quality of life, and reduce the frequency of medications required [3]. A significant reduction of body weight (>10%) can induce diabetes remission even among those with advanced disease and established diabetes complications [4,5].

In Malaysia, the prevalence of obesity among patients with T2D has been increasing each year, whereby 84% of the patients with T2D were recorded to be either overweight or obese in 2019 [6]. Unfortunately, studies have shown that a large proportion of them (59%-79%) are still not ready to act on losing weight [7,8]. Since they do not have the intention of losing weight, they would not be interested in practicing or acting upon the recommendations given by the primary care personnel and thus, are deprived of the benefit of losing weight.

Interventions in behavior modification have been proven as an important component in a successful weight control program, in addition to the dietary and physical activity components. A European guideline has shown that behavioral change can induce 5%-15% weight loss among overweight or obese individuals [9]. Theories on behavior change should be applied when developing any health intervention because it increases the likelihood of being more effective. Among the theories, the Transtheoretical Model (TTM) uniquely describes the behavior change process from not being ready (precontemplation, contemplation, and preparation) to the active stage (action and maintenance). Applying TTM may help researchers in understanding the behavioral issue and help to develop a tailored intervention based on the individualized readiness stage [10]. A systematic review has found that by implementing the stages of change of TTM, there were improvements in physical activity and dietary habits, specifically in terms of exercise duration and frequency, reduction in dietary fat intake, as well as increment in fruits and vegetable consumption [11]. Unfortunately, the current management of T2D does not identify those who are ready or not ready to make changes in their daily life [12]. Clearly, there is a need to help the large proportion of patients who are not ready to change to start taking action for weight loss.

Intervention in behavior modification should address the role of social environment on an individual’s readiness to lose weight. Weight loss-related behaviors, specifically healthy diet and physical activity are embedded in the social context, particularly the family context. Therefore, addressing behavior modification embedded in daily family life might be a promising approach to boost family support, thereby facilitating progress. Family support can be received in the form of companionship, emotions, information sharing, and instrumental assistance to facilitate the weight loss journey [13]. Integration with the family support component can lead to a more maintainable behavioral change, a better improvement of diabetes outcomes, as well as help to improve the health of family members [14,15].

Over the decades, web-based health technologies are increasingly used as a delivery mode for health promotion and prevention. The web-based platform will provide a good opportunity to improve the management of patients with T2D with obesity. Implementing web-based health promotion and prevention can widen the opportunity to reach specific target groups, lower the cost of implementation, and improve the health of the population [16]. It may overcome problems such as time constraints, privacy concerns, and the negative perception of being obese. Furthermore, web-based intervention can be delivered within a social system so that all members, for example, of a family can simultaneously and collectively take part in the obesity intervention and share their plans, goals, and progress [17]. To increase the efficiency of the interventions, the intervention can be coupled with tailored feedback and counseling [18]. Unfortunately, there is limited knowledge in the literature on web-based health intervention that has been developed based on the TTM targeting adults with T2D with obesity and integrating the family support component.

The objective of this trial is to develop and validate “Chance2Act,” an innovative web-based intervention grounded in the TTM, designed specifically to facilitate behavioral change in overweight or obese adults with T2D who are not ready to take action toward weight loss. Then, the effectiveness of the newly developed digital health intervention will be determined based on a nonrandomized controlled trial.

## Methods

### Overview

This study will be conducted in two phases, which are (1) phase 1: the development and validation of the Chance2Act intervention module and (2) phase 2: the nonrandomized controlled trial of the Chance2Act intervention.

### Phase 1: Content Development and Validation

Phase 1 of the study concerns the development and validation of the health intervention module. To get the initial ideas, framework, and justification for the selection of topics, a literature review and document analysis will be done. The content selection will be based on the key findings from the review of previous studies, the available local and international guidelines, as well as published reports, and available statistical data. The search sources will involve web-based databases, websites and printed materials (guidelines, pamphlets, posters, factsheets, reports, etc) that incorporate behavior change theories and family support components.

In addition, experts in related fields from different sectors (government, private, and nongovernmental organizations) will be invited for informal interview sessions to share experiences and give input for the new intervention. Further exploration will be conducted through informal interviews with overweight or obese adults with T2D, focusing on the knowledge, awareness, and practice of unhealthy behaviors, challenges, and facilitators for weight loss.

The contents of the health education module will be arranged according to the Process of Change construct of TTM. Then, the contents of the module will be drafted including the texts and graphics, as well as the formatting and layout for the website which acts as the medium of delivery for the health intervention. The local language (Malay language) will be used for the communication. The website will be arranged with consideration of the appropriate sequence. An attractive illustration will be used to ensure participants’ engagement and hence complete the entire package of the intervention module.

For the validation of the intervention module, 6 experts from relevant fields related to obesity and diabetes management will be selected to evaluate the newly developed health intervention module. The experts will consist of (1) an epidemiologist of noncommunicable diseases, (2) a health education expert, (3) a family medicine specialist, (4) a dietician, (5) a sports medicine specialist, and (6) a medical officer in-charge of the diabetes program in a health clinic. The Content Validity Index (CVI) will be analyzed to determine the relevance of the intervention content.

A face validation study will be conducted among overweight or obese adults with T2D and the public to determine the clarity, simplicity, and ambiguity of the intervention content. It will be quantified by using the Face Validity Index (FVI). After being proven to be valid to achieve the primary objective, the final version of Chance2Act Health Intervention will be ready to be used in phase 2: the nonrandomized controlled trial. Figure 1 illustrates the study flowchart for phase 1.

**Figure 1 figure1:**
[figure not shown]
Study flowchart for phase 1.

### Phase 2: Nonrandomized Controlled Trial

#### Study Setting

Phase 2 of the study will be conducted as a nonrandomized controlled trial, which is aimed to determine the effectiveness of the Chance2Act intervention. The study is expected to be conducted over 4 to 6 months, at 2 government health clinics in Pahang state, Malaysia. These 2 health clinics will be enrolled by the researcher and are expected to have similarities in terms of the sociodemographic background of the local community. The assignment into either the intervention or control group will be based on the health clinic where the participants are getting their treatment from. One health clinic will be assigned as the intervention arm whereas another clinic as the control arm. The study flowchart for phase 2 is summarized in Figure 2. This is an unblinded study with a parallel assignment (ie, intervention vs control [usual care] with an allocation ratio of 1:1). Blinding is not possible due to the nature of the intervention which is mainly health education.

To avoid contamination, the 2 health clinics will not be selected from neighboring localities. Access to the Chance2Act website will be restricted only to the registered participants and family members from the intervention arm. A username and password will be provided to log in to the website. The participants, family members, and the medical staff at the participating health clinics are not allowed to share any intervention material with a third party.

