#### Sample Size Calculation

The sample size was calculated using OpenEpi (version 3; Kelsey et al) open-source calculator for cross-sectional, cohort, and randomized control trials. To obtain 95% CI and 80% power of the study (α=.05), the minimum sample size required in each arm is 44 to achieve a 30% proportion difference postintervention [20]. Considering a 40% (n=21 participants) attrition rate, we aim for a total of 65 participants per arm.

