To determine the homogeneity between the intervention and control group, an independent *t* test and chi-square test will be used to compare the demographic characteristics of the participants. The ITT analysis will be applied to measure the effectiveness of the Chance2Act intervention on the primary and secondary outcomes. The analysis models are within-group differences and between-group differences. The Generalized Estimating Equations (GEE) will be used as statistical analysis. A *P* value of less than .05 is considered statistically significant with 95% CI. Interim analysis will be conducted at T1 which is estimated at week 5. However, only certain outcome measures will be analyzed as predetermined in the phase 2 study flowchart.

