### Strengths and Limitations

To our best knowledge, the Chance2Act intervention is the first web-based intervention that promotes behavior change, specifically designed for adults with T2D with obesity but not yet prepared to start losing weight. Developing an intervention for this population group is crucial, as a significant number (59%-79%) of them are not yet actively making weight loss efforts [7,8]. We hope that this intervention can contribute to better outcomes of obesity care in patients with T2D, thus, potentially leading to the metabolic benefits associated with weight loss.

In terms of the study design, the selection of a nonrandomized controlled trial method is acceptable due to the nature of the intervention given. Since the health interventions are delivered through a website, blinding of the study participants and researcher is not possible. The participants need to be aware of group assignments, thereby they will access the website and be involved in the intervention.

Another potential limitation that may arise during the study is that participants who do manifest interest are limited to patients with T2D with good digital literacy skills only. As a result, the findings of the study may not be applicable to a broader population, especially those with limited digital literacy. Digital literacy of the study participants may influence the conclusions concerning the uptake and attrition rate of the intervention.

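### With one chosen clinic per arm, the stated alpha, power, P values and CIs describe a treatment effect only if the clinic effect is zero, which the design cannot check

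*Protocol article*

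**What the plan says.** Study Setting sets arm by place of care: "The assignment into either the intervention or control group will be based on the health clinic where the participants are getting their treatment from". There are two clinics, both picked by the researcher, and "One health clinic will be assigned as the intervention arm whereas another clinic as the control arm". The clinics "are expected to have similarities in terms of the sociodemographic background of the local community", and they are deliberately kept apart: "To avoid contamination, the 2 health clinics will not be selected from neighboring localities". The same section describes phase 2 as a trial "which is aimed to determine the effectiveness of the Chance2Act intervention", and Principal Findings repeats that aim.

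Sample Size Calculation begins "To obtain 95% CI and 80% power of the study" and arrives at a minimum of 44 per arm for a 30-point difference in proportions, raised to 65 per arm for attrition. It mentions no ICC or design effect. Data Management and Statistical Analysis says "The Generalized Estimating Equations (GEE) will be used as statistical analysis", with P below .05 as the criterion and no mention of clinic.

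Three safeguards against imbalance are described: the expected sociodemographic similarity, purposive sampling for homogeneity (Study Population), and baseline comparison of demographics by t test and chi-square test (Data Management and Statistical Analysis). Strengths and Limitations says that "the selection of a nonrandomized controlled trial method is acceptable due to the nature of the intervention given", and supports this by saying that participants and researchers cannot be blinded. The further limitation it names is digital literacy.

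**The concern.** The unit of assignment is the clinic, and each arm has one. The sample size treats patients as independent, individually assigned observations. Staff, counselling practice and community can all differ between two non-neighbouring clinics. Control Group says that usual care follows each clinic's own schedule, so the comparator itself may be clinic-specific. All such differences enter the estimated treatment effect, and none of them enters its standard error.

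What is at stake is the main conclusion. A P value below .05 would show that these two clinics differ in the proportion of patients who become ready to act. It would not show why. The article nevertheless presents the result as determining effectiveness and, under Conclusions, as a possible basis for use in other settings.

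**Working it through.** **1. The plan's own figure.** Inputs from Sample Size Calculation: alpha .05 (two-sided assumed), power 80%, difference 0.30, Kelsey formula as implemented in OpenEpi. The two proportions are not given. For equal arms:

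n = (1.960 + 0.842)² × p̄(1 − p̄) × 2 / 0.30²

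At p̄ = 0.5: 7.849 × 0.25 × 2 / 0.09 = 43.6, so 44. The formula gives 44 for control rates from 0.30 to 0.40, and 44 is its maximum for a 30-point difference. The figure is consistent with an individual-level calculation and contains no hidden allowance for clustering.

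**2. Structure (no assumption needed).** A clinic term would be collinear with arm. Between-clinic degrees of freedom = 2 clinics − 2 arms = 0. The article does not state the GEE clustering unit, but neither choice helps. Clustered on participant, GEE ignores clinic. Clustered on clinic, it has two clusters, one per arm. Baseline adjustment for the readiness outcome does not help either: Eligibility Criteria admits only patients in a not-ready stage, so the ready/not-ready outcome is the same for everyone at entry. Clinic-specific change by week 9 stays merged with the intervention.

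**3. Illustration of size (ICC assumed; none is given in the document).** With m analysed per clinic:

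- variance inflation DE = 1 + (m − 1) × ICC
- multiplier for SE and CI width = √DE
- type I error of the unadjusted test = 2 × [1 − Φ(1.96/√DE)]
- power with the SE widened = Φ(2.802 × √(m/44)/√DE − 1.96)

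| m | ICC | DE | √DE | Type I error, unadjusted | Power, SE widened |
|---|---|---|---|---|---|
| 44 | 0 | 1.00 | 1.00 | 5.0% | 80% |
| 44 | 0.005 | 1.215 | 1.10 | 7.5% | 72% |
| 44 | 0.01 | 1.43 | 1.20 | 10.1% | 65% |
| 44 | 0.02 | 1.86 | 1.36 | 15.1% | 54% |
| 44 | 0.05 | 3.15 | 1.77 | 27.0% | 35% |
| 65 | 0 | 1.00 | 1.00 | 5.0% | 93% |
| 65 | 0.01 | 1.64 | 1.28 | 12.6% | 76% |
| 65 | 0.02 | 2.28 | 1.51 | 19.4% | 62% |
| 65 | 0.05 | 4.20 | 2.05 | 33.9% | 38% |

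The rows with m = 44 are the stated minimum. Those with m = 65 assume that everyone planned in Sample Size Calculation is analysed. A beta-binomial simulation at m = 44 gave type I errors of 10.8%, 16.0% and 28.5% at ICC 0.01, 0.02 and 0.05, close to the formula. The power column treats the ICC as known, which this design cannot supply.

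**4. The same in percentage points.** For two clinics treated identically, with an assumed readiness rate of 35%, the 95% range of their true difference is ±1.96 × √(2 × ICC × 0.35 × 0.65). That is about ±13, ±19 and ±30 points at ICC 0.01, 0.02 and 0.05. The last equals the whole target effect.

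**The case against.** The strongest reply is that the design is openly disclosed. The title calls the trial nonrandomised, and steps towards comparable groups are planned. This stands as far as it goes: nothing is concealed. But expected sociodemographic similarity, purposive sampling and baseline tests on demographics cannot balance staff, counselling or community, and they give no estimate of clinic variance.

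It is also fair that the ICCs are assumptions and that a condensed article may leave GEE details to another document. The figures above are illustrative for that reason. The zero degrees of freedom depend on neither the ICC nor the GEE specification.

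Three stronger readings are tempting but not supported:

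- A reader might infer that the type I error *is* above 5%. That holds only if a clinic effect exists. With none, 5% and 80% are right, but the trial cannot show which case applies.
- A reader might infer that contamination is why the investigators did not randomise. Study Setting gives contamination only as the reason for choosing non-neighbouring clinics. The sole justification offered for non-randomisation is the blinding argument.
- A reader might think that an ICC-widened interval repairs the analysis. It does not. An ICC treats clinic differences as random draws, whereas these clinics were chosen. Widening leaves any systematic shift in the estimate where it is.

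**Conclusion.** The concern stands in conditional form. Clinic and arm are completely confounded, and between-clinic variance is not estimable at any number of patients. The stated alpha, power, P values and CIs are therefore statements about the intervention only if the clinic effect is zero. An unqualified claim to determine effectiveness goes beyond what the design can support.

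The rationale in Strengths and Limitations does not hold: being unable to blind does not prevent randomisation. The section also leaves out the limitation that matters most.

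The structural conclusion rests on the document alone. Its numerical size rests on the assumed ICCs, a two-sided test and an exchangeable clinic effect. On those terms, at 44 per clinic and ICC 0.01 to 0.05, the nominal 5% becomes roughly 10% to 27%.

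**What to change.** 1. In Sample Size Calculation and in Data Management and Statistical Analysis, state that alpha, power, P values and CIs are conditional on no clinic effect and exclude between-clinic variation.
2. In Study Setting and Principal Findings, limit the conclusion to a difference between these two clinics, in place of a determination of effectiveness.
3. Add a sensitivity table for the primary estimate that multiplies its SE and CI width by √(1 + (m − 1) × ICC), with m the number analysed per clinic and assumed ICCs from 0.005 to 0.05. The square root matters: at m = 65 and ICC 0.05 the width multiplier is 2.05, while 4.20 is the variance factor. Note beneath the table that it does not correct systematic bias from differences between the chosen clinics.
4. In Strengths and Limitations, remove the blinding argument as the justification for non-randomisation, have the investigators give their own reason, and name clinic confounding as the main limitation.

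The cost is wording and one extra table, with no change to recruitment or data collection. The price is a weaker headline claim and a wider sensitivity interval.
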